  1. SECONDARY OBJECTIVES

1. To what extent can value of care variation in care be identified from ePROMs and ePREMs surveys?

- What is the share of suspected low-value care and suspected high-value care in Germany, per indication and in subgroups?
- How do ePROM and ePREM results differ according to age, gender, indication, city/state, healthcare system utilization (changes in frequency of outpatient practitioner attendance, prescriptions, hospitalizations, etc.), and DMP participation?
- Can ePROMs and ePREMs function as an early warning signal for deteriorating chronic conditions or adverse events such as hospital admission?

1. What are the benefits or drawbacks of PRO feedback (outcome reports) sent to patients?

- Are the PRO value reports understandable to patients?
- Can PRO feedback function as a positive nudge (lead to positive behavioral changes e.g., healthier or more active lifestyle, more active participation in medical treatment, actively approaching treating physicians in the office setting)?
- Are there any negative emotional reactions when receiving PRO feedback that shows values worse than those of a comparable group?

1. Background/Introduction

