   1. STUDY DESIGN

The study is an observational prospective cohort study with patients of four chronic disease areas with existing DMPs (asthma, chronic obstructive pulmonary disease (COPD), diabetes (type 1 and type 2) and coronary artery disease) with two sub-cohorts (DMP and non-DMP) for each disease.

- Type of control: none / group matched BARMER insurees (matching criteria: disease area, gender, age group)
- Level and method of blinding: none
- Method of treatment assignment: stratified randomized selection of study population
- Number of subjects: 200,000 patients invited (50,000 per chronic indication and about 25,000 in each sub-cohort)
- Duration of study: one year (four quarterly survey periods)

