An initial invitation letter is sent to 200,000 insured individuals, 50,000 of each of the selected chronic conditions (about 25,000 per sub-cohort). Diabetes type 1 and type 2 are considered jointly as there is no differentiation in the selected PROMs. The patients of all chronic diseases are allocated to groups based on their participation in DMP (DMP or non-DMP group). Prior experiences suggest that around 30% of patients react to invitations to participate in research by their insurer [29-31]. Two-thirds of initial participants are expected to allow follow-up contacts and around 40% of these patients will continue participating in all the follow-up surveys after receiving reminders for each task. Therefore, after accounting for non-participants and participants with no complete survey data we expect a complete data set for 16,000 participants. However, the first research question will investigate response rates as there is no evidence on this population yet.

- 1. STUDY PROCEDURE

Eligible participants will be participating in the study for a maximum of four quarters, starting with the first access of the digital questionnaires followed by quarterly digital surveys split into several tasks. To start the survey, participants register with their study pseudonyms and share personal information, e.g., basic demographics and identification data. Each survey period contains four tasks to be completed by participants defined as sets of questions that each will take five to ten minutes to complete. The participants are invited to answer PROM and PREM surveys.
[figure not shown]

*Figure 1: Study design: Participants’ timeline and tasks*

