**The secondary data, retrieved from the participating health insurance BARMER includes the following data points:**

- Personal data: age, sex, death date (if applicable), insurance times, region of residence
- Disease management program participation: program type, participation times
- Outpatient care data: date of attendance, invoiced fee schedule items, practitioner’s specialty, diagnoses (ICD-10-GM), procedures (OPS)
- Prescriptions of medications: drug identifier, no of prescriptions, date of prescription, prescribing practitioners’ specialty, anatomic-therapeutic-code (ATC), dosage (defined daily dosage - DDD), costs
- Allied health professions (podiatric, dietary, speech and language, ergo- and physiotherapy): date of prescription, indication, diagnosis (ICD-10-GM), prescription type, remedy type, first/last date of remedy application, number of applications, prescribing practitioners’ specialty, costs
- Assistive technology: date of prescription, unique identifier of assistive technology, first/last date of application, number of applications, prescribing practitioners’ specialty, costs
- Inpatient hospital stays: clinic identifier, date of admission/discharge, admission/discharge mode, discharging departments’ specialty, diagnoses (ICD-10-GM), procedures (OPS)
- Hospital care: clinic identifier, date of entry/discharge, diagnoses (ICD-10-GM), procedures (OPS), fee schedule items, costs
- Work incapacitation: first/last date of work incapacitation, diagnosis (ICD-10-GM), days of wage-replacement-benefits, costs of wage-replacement-benefits
- Transportation: prescribing practitioner with specialty, prescription date, first/last day and number of service(s), fee schedule items, costs
- Household assistance: prescribing practitioner, prescription date, first/last day and number of service(s), fee schedule items, costs
- Short-term nursing care: prescribing practitioner, prescription date, first/last day and number of service(s), fee schedule items, costs
- Rehabilitation: prescribing practitioner, first/last day of rehabilitation, type of rehabilitation (inpatient/outpatient, mobile, combinations), funding agency, diagnoses (ICD-10-GM), costs
- Long-term care benefits: level of care, first/last date of the current level of care, care type, first/last date of care benefits, costs

1. Populations of Analysis

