Based on the combination of PROMs, PREMs and health care system utilization measured as costs, a value-based healthcare cube is introduced. PROM and PREM scores function as outcome dimensions and healthcare system utilization as cost dimension. Costs are hence added as new axis inside the framework (see Figure 5).

[figure not shown]

*Figure 5: Assessment of Value-Based Healthcare - Framework*

The newly introduced value-based healthcare cube allows the measurement of high-value and low-value care. Along the previously defined areas of suspected high- and low-value care (see Figure 4 and 5), the cube can be subdivided into 27 segments (see Figure 6). High-value and low-value care will be investigated based on the following criteria:

- High-value indication in both dimensions (high patient-relevant indicators (PROMs/PREMs) **at** low costs) (Figure 6 – dark green area)
- High-value indication in at least one dimension (high patient-relevant indicators (PROMs/PREMs) **or** low costs) (Figure 6 – light green area)
- Low-value indication in at least one dimension (low patient-relevant indicators (PROMs/PREMs) **or** high costs) (Figure 6 – light red area)
- Low-value indication in both dimensions (low patient-relevant indicators (PROMs/PREMs) **at** high costs) (Figure 6 – dark red area)

The value of care dimensions will be summarized into high- versus low-value care as the broad definition and into high two-sided, high one-sided, low one-sided and low two-sided value care as narrow definition. For both categorizations the frequency as well as the variation per subgroups (e.g. region, DMP etc.) will be analyzed.

[figure not shown]

*Figure 6: Assessment of Value-Based Healthcare – Framework distinguishing between high- and low-value care*

*Outcome and experience variation*

Mean change in PROM and PREM-index (sub-)scores overall and per subgroup (see 5.1 and 4.3) per disease area over time:

- Average per survey period
- Consistency over time (test-retest reliability)

Meaningful change / Minimally clinical important difference (MCID) in PROM index (sub-)scores overall and per subgroup (see 5.1 and 4.3) per disease area over time:

- Average per survey period
- Consistency over time (test-retest reliability)

*Hospital admission risk based on PROMs/PREMs and patient characteristics*

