- Using machine learning predictive models (long-short-term memory deep learning network for time trend classification, random forest, logistic regression, decision tree and/or support vector machine) to identify admission risk in Q3 and Q4 based on PROMs/PREMs in Q1 and Q2

*PRO feedback*

- Mainly: Statistically significant change in at least one of the health care behavior dimensions (see 4.2) and comparison of participants who opened the report vs. those who did not, using logistic regression (change/no change)
  - Physical activity: Shift of participants to a higher category
  - Nutrition: Shift of participants to “More healthy” from any other category
  - Tobacco: Shift of participants to a lower category
  - Alcohol: Shift of participants to a lower category
  - Sleep: Share of stable participants (no significant variation in sleep duration)
- Secondly: Descriptive exploratory analysis of the rates of the following two evaluation dimensions and statistically significant differences in subgroups (see 5.1 and 4.3):
  - Understandability
  - Helpfulness
  - Emotional change

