**Data analysis**

- Check for normality using the Shapiro–Wilk test
- Check for intraclass correlation using intraclass correlation coefficients
- Analyze missing data
- Descriptive statistics of patient and treatment characteristics
- Time series analysis
- Parametric and non-parametric methods
- Statistical tests depending on normality for the primary and secondary outcomes to compare:
  - Responders vs. non-responders (to the nudge)
  - DMP vs non-DMP members
- Linear and logistic regressions controlling for:
  - Significant patient characteristics
  - Significant other collected variables depending on the research question

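### The hospital-admission models name no reference model without PROMs/PREMs, so as written they show that a combined model predicts admission but not what ePROMs/ePREMs contribute

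*Protocol*

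**What the plan says.** Section 1.2 of the protocol puts the question this way: "Can ePROMs and ePREMs function as an early warning signal for deteriorating chronic conditions or adverse events such as hospital admission". The subject of the question is the questionnaires, not a risk model in general.

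Section 5.2, under Secondary Outcomes, answers it with one heading and one bullet. The heading is "Hospital admission risk based on PROMs/PREMs and patient characteristics". The bullet lists a long short-term memory network, then "random forest, logistic regression, decision tree and/or support vector machine", to be used "to identify admission risk in Q3 and Q4 based on PROMs/PREMs in Q1 and Q2". These are alternative model types. No alternative predictor sets are named.

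Two other places bear on the point. The claims listed in section 2.6 include "Inpatient hospital stays: clinic identifier, date of admission/discharge", together with outpatient care, prescriptions and costs. The general Data analysis list at the end of section 5.2 provides for linear and logistic regressions that control for significant patient characteristics and "Significant other collected variables depending on the research question". It does not tie this to the admission models.

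**The concern.** Patients with poor scores tend also to be older, sicker and more often in hospital already, and those features predict the next admission by themselves. If they are in the model, or are merely correlated with the scores, good discrimination says nothing about where it comes from. Without a model that omits PROMs/PREMs, a useful questionnaire and one that only restates known severity can give the same headline figure.

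At stake is a possible conclusion that ePROMs work as a warning signal when the result supports only the statement that admission is predictable. The insurer already holds the claims, so the difference matters for whether quarterly surveys are worth running for this purpose.

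**Working it through.** **The plan's own figure.** The protocol gives no admission rate, target AUC or power for this analysis. Its only related number is the expected complete data set in section 2.5, which reproduces: 200,000 × 0.30 = 60,000 responders; × 2/3 = 40,000 allowing follow-up; × 0.40 = 16,000. Spread evenly over four diseases, that is 4,000 each. With an assumed Q3+Q4 admission rate of 5% to 20%, there would be 800 to 3,200 patients admitted in all, and 200 to 800 per disease. Fitting two nested models is therefore feasible with the planned data.

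**Illustration.** All inputs below are assumptions. Each replicate has 16,000 training and 16,000 test patients, and there are 10 replicates.

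- logit P(admission) = m + 1.0 × claims score + 0.3 × characteristic + b × PROM, with m set so that 10% are admitted.
- PROM = ρ × claims score + √(1 − ρ²) × noise, all variables standardised.
- ρ = 0.3, 0.5, 0.7; b = 0, 0.2, 0.4.

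Mean out-of-sample AUC (gains come from unrounded values):

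| ρ | b | Char. | Char. + PROM | Char. + claims | All three | Gain from PROM over char. + claims |
|---|---|---|---|---|---|---|
| 0.3 | 0 | 0.574 | 0.608 | 0.756 | 0.756 | 0.000 |
| 0.3 | 0.2 | 0.576 | 0.647 | 0.770 | 0.773 | 0.004 |
| 0.3 | 0.4 | 0.575 | 0.687 | 0.777 | 0.790 | 0.014 |
| 0.5 | 0 | 0.577 | 0.648 | 0.759 | 0.759 | 0.000 |
| 0.5 | 0.2 | 0.572 | 0.684 | 0.773 | 0.776 | 0.003 |
| 0.5 | 0.4 | 0.576 | 0.724 | 0.787 | 0.797 | 0.010 |
| 0.7 | 0 | 0.579 | 0.691 | 0.760 | 0.760 | 0.000 |
| 0.7 | 0.2 | 0.572 | 0.730 | 0.782 | 0.784 | 0.002 |
| 0.7 | 0.4 | 0.572 | 0.766 | 0.804 | 0.810 | 0.006 |

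**Reading it against the plan.** The protocol does not settle whether patient characteristics in the admission heading include healthcare utilization, so both cases need checking.

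- If utilization is included, the planned model is the column with all three. With b = 0 it reaches 0.756 to 0.760, and none of that comes from the PROM.
- If it is not included, the planned model is characteristics plus PROM. Two very different truths then look alike: 0.691 (ρ = 0.7, b = 0) and 0.687 (ρ = 0.3, b = 0.4). The gains over characteristics and claims are 0.000 and 0.014.
- A reference with characteristics only would help but can mislead. With b = 0 the PROM appears to gain 0.608 − 0.574 = 0.034 up to 0.691 − 0.579 = 0.112, all of it borrowed from risk visible in claims.

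In either case the single AUC from the planned model does not isolate the PROM. The contrast between the nested models does.

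**The case against.** The strongest reply is that this is detail for a statistical analysis plan. Predictor sets and validation of a secondary machine-learning analysis are often settled there, and that document is not at hand. Nothing in the protocol prevents a nested comparison. This stands against saying that the trial cannot show a contribution; the supportable statement is that the analysis as written does not. It does not remove the point, because the protocol does state the predictors, the algorithms and the window, and the comparison it sets out is between algorithms.

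Second, the plan is not based on PROMs alone. The Primary Outcomes text in section 5.2 counts healthcare utilization among patient characteristics, and the Data analysis list allows adjusted regressions. This is fair, and it rules out judging the plan by the AUC of a PROM-only model. But more predictors in one model make it harder to credit the questionnaires. The adjustment is not assigned to this analysis, and an adjusted association is not a measure of predictive gain.

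Third, value beyond claims is not a standard the protocol sets. That is correct; the choice of claims for the reference model is a recommendation. Even on the protocol's own question, though, some model without PROMs/PREMs is needed.

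A reader might also infer two stronger criticisms:

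- *That the fixed window is an error, or is the reason added value goes unshown.* With and without PROMs/PREMs can be compared inside one window. The window also has a rationale: a trend needs two measurements, and predictors come before outcomes.
- *That everyone without a Q2 survey is excluded.* No complete-case rule is stated. Section 3 applies all analyses to participants who have not withdrawn consent, and section 5.1 plans missForest imputation of applicable outcomes for the second research question. Whether this covers Q2 scores is unclear, so exclusion is not established.

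**Conclusion.** The point holds in limited form. Section 5.2 predicts admission from PROMs/PREMs and patient characteristics together and names no model without PROMs/PREMs. It can therefore support a statement about the combined model but not the statement that section 1.2 asks for.

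The documents allow no numerical size for this trial. The simulated AUCs rest on assumed admission risk, effect sizes and correlations, and the zero gain at b = 0 follows from how the data were generated. They show only that the planned output does not tell the cases apart. The documents do not support saying that the study is unable to answer the question, that the window is wrong, or that follow-up losses bias this analysis.

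Severity is minor: this is one sub-question of a secondary objective, and the protocol ties no threshold or decision to it.

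**What to change.** In section 5.2, under the hospital-admission heading, pre-specify two nested models within the stated Q1/Q2 to Q3/Q4 window. Use the same patients, the same training/test split and the same algorithm for both.

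1. Reference: patient characteristics and claims up to the prediction date (age, sex, disease, DMP status, earlier admissions, medication, cost).
2. Extended: the reference plus PROMs/PREMs from Q1 and Q2.

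State that the early-warning question is judged by the difference in held-out discrimination and calibration, with a confidence interval, and not by the AUC of the extended model alone.

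Optionally, add a supplementary survey-to-next-quarter analysis (Q1 to Q2, Q2 to Q3, Q3 to Q4) to describe lead time. This is an extension, not a correction. It would need all records of a patient kept on one side of the split, it still requires the survey at each step, and its first step has no score change to use.

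The cost is wording and modest extra modelling on data already collected. The incremental figure will probably look small beside a stand-alone AUC; in the illustration, a real PROM effect gave a gain of only 0.002 to 0.014.

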  1. INTERVENTION

In addition to filling out the survey questions at four points in time (intervention 1), all participants will receive PRO feedback as a potential nudge (intervention 2). The PRO feedback will be a pdf report sent via email and available in their study participant profile, which graphically (line charts) shows the patients’ individual generic and disease-specific health status in comparison to the individual peer group. In addition to the visual feedback, the results will shortly be explained on the same page. The description will cover whether patient-individual PRO scores are better or worse compared to the peer group, and for longitudinal values, whether patient-related changes improved or worsened. Additional details on the scores, sub-scores, and calculations are shared with the patients on the following pages of the report. Peer groups are classified according to their disease, gender, and age group. The peer group is created based on individuals who have replied to the previous survey and will only be displayed if the group consists of at least four individuals. This threshold is set by the German General Data Protection Regulation. The report refers to the patients’ physicians as the main contact to discuss the results or in case of questions.

- 1. SAMPLE SIZE

The sample is drawn stratified randomly from insured patients of one large German statutory health insurance with about 9 million insured persons (of about 73 million statutorily insured persons in total in Germany) according to their diagnosis and/or disease management program status. A one-to-one matching of participants of one DMP with non-participants of a DMP but with the same proven diagnosis according to the ICD-10-GM system is made. Further stratification criteria are age group, gender, and health system utilization.

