As shown in Figure 1, the first point of contact will be a letter from the insurance to insured individuals with chronic diseases, who can then sign into the digital study via a QR code or link. For each of the different disease areas, a distinct care path is opened, with a sign-in process followed by selected PROMs and PREMs. The study covers a timeframe of one year with four overarching time intervals with dedicated questions. These are split into smaller tasks to facilitate the answering process for participants. The time intervals are split into smaller tasks to facilitate the answering process for participants. A few weeks after responding to the first set of questions (A & B), patients will receive a report with their individual PROM scores compared to a peer group, the PRO feedback (C). From the second interval onwards, patients will also receive the PRO feedback in a longitudinal visualization. Lastly, following the PRO feedback participants will be surveyed regarding their health behavior (D).

Figure 2 presents the questionnaires that will be used in the study per chronic disease group. PROM surveys include generic as well as disease-specific PROMs. The participants will receive individual reports on their patient-specific and peer group outcomes (PRO feedback) and will be asked about the comprehensibility of the report. Following the report, the participants receive a set of questions regarding the report’s comprehensibility and their health-related behavior.

[figure not shown]

*Figure 2: Survey items in the PROMchronic trial*

The primary data collected in this study is hence:

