**Patient reported indicators:**

- Generic PROM index score: PROMIS PROPr is a preference-based score which combines seven PROMIS domains of health status into one score (cognitive function, depression, fatigue, pain, physical function, sleep, social roles)
- Disease-specific PROM index scores for each chronic disease

Asthma: Asthma Impairment and Risk Questionnaire (AIRQ) score

COPD: Clinical COPD Questionnaire (CCQ) score

Diabetes: Problem Areas in Diabetes (PAID-5) score

Coronary artery disease: Seattle Angina Questionnaire (SAQ-7) score and Rose Dyspnea Scale (RDS) score

- PREM index score: Responsiveness of the health care system
- Looked at PRO feedback
- Comprehensibility of PRO feedback
- Helpfulness of PRO feedback
- Emotional reaction to PRO feedback
- Discussion of PRO feedback with physician(s)
- Health behavior in five dimensions:

Physical activity

Nutrition

Tobacco consumption

Alcohol consumption

Sleep duration

- Plans to change health behavior in the future
- Trigger for health behavioral change
- Overall health improvement
- Disease-specific health improvement

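### The main PRO-feedback comparison ties neither report opening nor behaviour change to a survey period; if both are coded as "ever", uneven follow-up alone can produce an association.

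*Protocol*

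**What the plan says.** Section 5.2, under PRO feedback, names as the main analysis "Statistically significant change in at least one of the health care behavior dimensions", with a "comparison of participants who opened the report vs. those who did not, using logistic regression (change/no change". The unit is the participant, the report is in the singular, and no survey period is attached to either variable. Four behaviours count a shift in a stated direction. The fifth is scored the other way: "Sleep: Share of stable participants (no significant variation in sleep duration".

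Section 2.1 sets "Duration of study: one year (four quarterly survey periods". Section 2.6 repeats the feedback ("From the second interval onwards, patients will also receive the PRO feedback in a longitudinal visualization") and places a behaviour survey (D) after it. Opening is listed among the patient-reported indicators as "Looked at PRO feedback", with no rule for combining it over periods. Section 2.4 states that "all participants will receive PRO feedback as a potential nudge", so the unexposed group consists of those who chose not to open.

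Section 2.5 expects that "around 40% of these patients will continue participating in all the follow-up surveys after receiving reminders for each task". Section 3 puts everyone who took part, apart from consent withdrawals, into all analyses.

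**The concern.** A participant with m completed periods has up to m reports to open and m − 1 intervals in which behaviour can shift. Reduced to one yes/no exposure and one yes/no outcome, both chances rise with m. Number of periods completed then acts as a common cause of being classed as opened and being classed as changed. This needs no difference in motivation, so adjusting for age, sex or disease does not in itself remove it.

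At stake is the main evidence on whether the feedback works as a nudge. Part of a reported effect could be an artefact of how long people stayed in the study.

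**Working it through.** **1. The protocol's funnel (section 2.5).** 200,000 × 0.30 = 60,000 initial participants; × 2/3 = 40,000 followed; × 0.40 = 16,000 complete. The stated 16,000 is reproduced. Hence 40,000 − 16,000 = 24,000 followed participants miss at least one survey.

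**2. Assumptions, not in the protocol.** The 24,000 split equally into 8,000 each with 1, 2 and 3 periods. Those with 1 period cannot show a change and are left out. The chance of opening each report is 0.5, independent between periods; the chance of a shift in each interval is 0.2; the report has no effect.

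**3. Ever/ever coding.** P(ever opened) = 1 − (1 − 0.5)^m and P(ever changed) = 1 − (1 − 0.2)^(m−1), independent given m.

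| m | n | P(opened) | P(changed) | openers (changed) | non-openers (changed) |
|---|---|---|---|---|---|
| 2 | 8,000 | 0.750 | 0.200 | 6,000 (1,200) | 2,000 (400) |
| 3 | 8,000 | 0.875 | 0.360 | 7,000 (2,520) | 1,000 (360) |
| 4 | 16,000 | 0.9375 | 0.488 | 15,000 (7,320) | 1,000 (488) |
| Sum | 32,000 | | | 28,000 (11,040) | 4,000 (1,248) |

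Changed: 11,040/28,000 = 39.4% against 1,248/4,000 = 31.2%. OR = (11,040 × 2,752)/(16,960 × 1,248) = 1.44, z about 10. Within each row the two groups have the same change rate; the association comes only from pooling the rows.

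**4. Range.** With opening 0.3 to 0.7 and shift 0.1 to 0.3, the OR is 1.22 to 1.84. At the two-sided 5% level of section 5.1, the chance of a false positive is 80–100% in a group of 8,000 and 29–85% in a group of 2,000.

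**5. What shrinks or removes it** (otherwise as in step 2):
- Opening correlated within person (beta-binomial, assumed): correlation 0.5 gives OR 1.10, 0.7 gives 1.055, 0.9 gives 1.02, and 1 gives 1.00. The false-positive chance in 8,000 people falls to 50%, 20%, 7% and 5%.
- All 24,000 incomplete participants answer three surveys: OR 1.09, or 1.06 to 1.21 over opening 0.3 to 0.8 and shift 0.1 to 0.4.
- Full responders only, or one report with one fixed pair of surveys: OR 1.00.

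**6. Sleep.** If stability means no change in any interval, the table is inverted: OR = 1/1.44 = 0.70.

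**7. Remedies under the null.** One simulated data set of 40,000 (2, 3 and 4 surveys for 12,000, 12,000 and 16,000; same rates) gave a crude OR of 1.40 (95% CI 1.32–1.49). Adjusted for number of surveys it was 0.98 (0.92–1.05). With opening linked to change in the next interval it was 0.99 (0.95–1.02). In a separate simulation of 400 replicates, the interval-level comparison with the report delivered between the two surveys rejected in 3.8%, 6.8% and 2.0% at full, quarter and one-sixteenth size.

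**The case against.** The strongest reply is that ever/ever coding is nowhere written. The phrase about at least one refers to behaviour dimensions, not periods, and a survey item on looking at the report, followed by a behaviour survey, could equally be linked period by period. A SAP, not shown here, could settle this. Section 5.2 also lists time series analysis, intraclass correlation and regressions controlling for significant other variables. Section 4.2 already defines first, regular and full responders. Section 5.1 imputes applicable outcomes for this research question, which could change the number of intervals per person.

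Much of this stands. The bias is conditional on a coding, and independent opening is an assumption that favours a large figure; people with settled habits produce much less. How imputation would act cannot be determined from the text.

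It does not dispose of the point. The protocol itself fixes a participant-level contrast with one binary exposure and one binary outcome, and ever/ever is a natural way to fill those from repeated data. Elsewhere section 5.2 does refer to periods: at least two survey periods for value of care, averages per period, and Q1 and Q2 predicting Q3 and Q4. The generic methods are not tied to this comparison, and number of surveys completed is not named as a covariate.

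A reader might infer that the planned analysis is bound to give a false positive. The documents do not support that: they state no such coding, the opening and dropout patterns are unknown, and for sleep the distortion runs the other way.

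**Conclusion.** The point holds in conditional form. The main feedback comparison does not say which report defines opening or between which surveys change is measured, and completed periods will vary widely on the protocol's own figures. Under ever/ever coding and a report with no effect, the OR is about 1.2 to 1.8 if opening is independent between periods and dropout is spread over them. It is about 1.0 to 1.1 if opening is strongly persistent or nearly all incomplete participants answer three surveys. With one report and one fixed pair of surveys the mechanism is absent. The direction is positive for the four shift dimensions and reversed for sleep stability. Opening rates, shift rates and the dropout split are all assumed. The wording should be changed, because this is the stated main analysis of the nudge question and the safer analysis uses data already planned.

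**What to change.** In section 5.2, define exposure as opening a specific report, and outcome as the shift between the behaviour surveys on either side of it: D in period k to D in period k+1, with report k+1 as exposure. Fit a logistic model with survey period as a categorical term and allowance for repeated intervals within participant (GEE with clustered errors, or a random intercept). Add opening of earlier reports as a covariate to allow for carry-over. At minimum, condition the participant-level model on the number of behaviour surveys completed.

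The cost is wording and a more complex model, provided that the opening item is recorded in each period. Participants with a single behaviour survey do not contribute. The first report has no behaviour survey before it, so it enters only as earlier exposure. The fix does not deal with self-selection: every participant is sent the report and openers choose to open it, so the result should be reported as an observational association.
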